### Time to the first of the following clinical outcomes myocardial infarction, stroke, peripheral amputation, or death

4.5

We consider a 12.5% risk of experiencing one or more of the following outcomes: non-fatal myocardial infarction, stroke, peripheral amputation, or death in the placebo group [25], an alpha of 0.001, and a hazard ratio reduction of 30%. For the metformin versus placebo comparison, we will only have 2% power to confirm or reject a hazard ratio reduction of 30%. For each of the three pairwise insulin comparisons, we estimate that we will only have 1.2% power to confirm or reject a hazard ratio reduction of 30%.

### Time to cardiovascular death

4.6

We consider a 3.8% risk of experiencing death from cardiovascular disease in the placebo group [25], an alpha of 0.001, and a hazard ratio reduction of 30%. For the metformin versus placebo comparison, we will have almost 0% power to confirm or reject a hazard ratio reduction of 30%. For each of the three pairwise insulin comparisons, we estimate that we will have 0% power to confirm or reject a hazard ratio reduction of 30%.

We plan to present the results of these three cardiovascular outcomes in the Supplemental material because of the low statistical power.

## Stratification and design variables

5

We used three stratification variables in the randomisation: age >65 years (yes/no), insulin treatment at trial entry (yes/no), and treatment at Steno Diabetes Center (yes/no) [1].

Other design variables were sex (male/female), prior cardiovascular disease (yes/no), statin treatment at entry (yes/no), and glutamic acid decarboxylase antibodies at entry (positive/negative) [1].

## Definition of populations the following populations will be analysed

6

•A modified intention-to-treat population. This population includes all randomised participants except randomised participants who did not fulfil the inclusion criteria; randomised participants fulfilling one or more exclusion criteria; or randomised participants who did not receive any of the planned interventions [1].•A per-protocol population. This population includes all those included in the modified intention-to-treat population, except participants who did not attend more than four out of the planned six visits following randomisation [1].

## Handling of missing data

7

We will handle missing data according to the recommendation by Jakobsen and colleagues [26]. In short, we will consider using multiple imputation if it is not valid to ignore missing data [26]. If multiple imputation is used, then the primary result of the trial will be based on these data [26]. To take account of the possibility that data may be ‘missing not at random’, we will use a best-worst and worst-best case scenario as sensitivity analyses, which will assess the potential impact of the missing data on the trial results [26]. In the ’best-worst case’ scenario it is assumed that all patients lost to follow-up in the experimental group have had a beneficial outcome; and all those with missing outcomes in the control group have had a harmful outcome [26]. Conversely, in the ’worst-best case’ scenario, it is assumed that all patients who were lost to follow-up in the experimental group have had a harmful outcome; and that all those lost to follow-up in the control group have had a beneficial outcome [26]. When continuous outcomes are analysed, a ‘beneficial outcome’ will be defined as the group mean plus two SDs of the group mean, and a ‘harmful outcome’ will be defined as the group mean minus two SDs of the group mean for ‘best-worst case’ imputation [26].

When assessing quality of life and patient satisfaction, we will in secondary analyses assign the value ‘0’ for participants who died during the 18-months trial period.

We do not expect any missing values for the time to a cardiovascular outcome as all deaths and admissions to Danish hospitals are registered in the Civil Registry and the National Patient Registry and were adjudicated for clinical events by the blinded adjudication committee [2].

We will use the three stratification variables used in the randomisation and the four predefined design variables during the multiple imputation procedure to estimate the missing values, i.e. age >65 years (yes/no), insulin treatment at trial entry (yes/no), and treatment at Steno Diabetes Center (yes/no) as well as sex (male/female), prior cardiovascular disease (yes/no), statin treatment at baseline (yes/no), and glutamic acid decarboxylase antibodies (positive/negative) [26].

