### Short Form Health Survey (SF-36)

4.1

We consider 4 points as the minimal clinically relevant difference for SF-36 [14,[16], [17], [18], [19], [20], [21]], an alpha of 0.001, and a standard deviation (SD) of 9.5 points [12]. For the metformin versus placebo comparison, we will have a power of 83.0% to confirm or reject a 4-point increase on the SF-36. For each of the three pairwise insulin comparisons, we will have a power of 56.3% to confirm or reject a 4-point increase on the SF-36.

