## Strengths

13

This statistical analysis plan has a number of strengths. The overall trial methodology has been pre-defined, we take problems with multiplicity and other risks of random errors into account, use validated statistical methods, and we systematically test for the underlying statistical assumptions [1,14,28]. Furthermore, we will analyse data in accordance to the modified intention-to-treat principle and, if necessary, use multiple imputations, and a best-worst/worst-best case scenario to assess the potential impact of the missing data on the results [26]. We will use the five-step procedure proposed by Jakobsen and colleagues to assess whether the thresholds for statistical and clinical significance are crossed [14].

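### The two missing-data scenarios for the questionnaires are outer bounds only: from about 10% missing per arm they conflict for true effects of 0 and 4 points alike, with nothing planned in between

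*Protocol article*

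**What the plan says.** Section 7 (Handling of missing data) sets out the approach in three parts.

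- Multiple imputation is conditional: "we will consider using multiple imputation if it is not valid to ignore missing data". The imputation uses the three stratification variables and the four design variables.
- The possibility that scores are absent for reasons tied to their own values is covered as follows: "we will use a best-worst and worst-best case scenario as sensitivity analyses, which will assess the potential impact of the missing data on the trial". For continuous scores the favourable value is set by this rule: "a ‘beneficial outcome’ will be defined as the group mean plus two SDs of the group mean". The unfavourable value lies the same distance below. The two arms are pushed in opposite directions, and the worst-best case is the mirror image.
- A separate secondary analysis assigns zero "for participants who died during the 18-months trial period".

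No other general analysis for data missing not at random is named. Section 13 (Strengths) counts the scenarios in the plan's favour: "a best-worst/worst-best case scenario to assess the potential impact of the missing data on the results".

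The yardstick for the size of an effect is in section 4.1: "We consider 4 points as the minimal clinically relevant difference for SF-36", with an SD of 9.5. Sections 4.2 and 4.3 use 4 points and an SD of 9 for the two satisfaction questionnaires.

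**The concern.** Each imputed value lies 2 × 9.5 = 19 points from its group mean on the SF-36 (18 points on the other two scales). That is more than four times the difference the plan calls clinically relevant. The resulting movement in the treatment comparison depends on how much is missing and on the SD, not on the effect. With moderate missingness the pair of scenarios will therefore say that missing data could change the answer, both for a trial with no effect and for one with exactly the effect the power section is built on.

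Section 31 of the argument is simple to state: section 11 gives the questionnaire outcomes the most emphasis, and these scenarios are the only general check on informative non-response for them. If the two bounds disagree, a reader of either planned paper cannot tell from them whether a small or only an extreme departure from the imputation assumptions would change the conclusion.

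There is also a wording problem. Read literally, an SD of a group mean is a standard error, which would make the same check very mild.

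**Working it through.** **Inputs from the article.** SD 9.5 for SF-36 and 9 for the other scales; relevant difference 4 points; 206 per arm for metformin against placebo and 137 per arm for an insulin pair (sections 4 to 4.3). Alpha is 0.001 for power (section 4) and 0.01 for Trial Sequential Analysis (section 8.1).

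**Assumptions.** The article gives no missing rate, so m is varied and taken as equal in both arms. The simulations also assume a baseline correlation of 0.5.

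**The plan's own figures.** With two-sided alpha 0.001, the standard error for SF-36 is 9.5 × √(2/206) = 0.936 and 4/0.936 = 4.27. The noncentral t gives 83.0% power, as stated. The other stated powers (56.3%, 88.3%, 63.7%) also reproduce, so the inputs are being read as intended.

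**Shift.** Replacing a share m of one arm by its mean + 2 SD raises that arm's mean by 2 × SD × m. The other arm falls by the same amount, so the difference moves by 4 × SD × m = 38m points for SF-36:

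| Missing per arm | Shift (points) |
|---|---|
| 2% | 0.76 |
| 5% | 1.9 |
| 10% | 3.8 |
| 15% | 5.7 |
| 20% | 7.6 |

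The shift equals 4 points at m = 4/38 = 10.5% (4/36 = 11.1% when the SD is 9).

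**Where the verdicts part.** After imputation the within-arm variance is SD² × [(1 − m) + 4m − 4m²]. Setting the shifted difference against its critical value, without baseline adjustment, gives:

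- True difference 0: the two scenarios become significant in opposite directions above m = 6.9% (alpha 0.01) or 9.0% (alpha 0.001) with 206 per arm, and above 8.6% or 11.3% with 137 per arm.
- True difference 4, 206 per arm: the worst-best case loses significance above m = 3.8% (alpha 0.01) or 2.2% (alpha 0.001).

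**Simulation of the baseline-adjusted regression, alpha 0.01.** Share of trials in which both scenarios give the same verdict:

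- 206 per arm, true difference 0: 91% at 2% missing, 41% at 5%, 0% at 10%.
- 206 per arm, true difference 4: 94% at 2%, 42% at 5%, 0.2% at 10%.
- 206 per arm, true difference 6: 98.5% at 5%, 33% at 10%, 1% at 15%.
- 206 per arm, true difference 8: 97% at 10%, 34% at 15%.
- 137 per arm, true difference 0: 93.5% at 2%, 61.5% at 5%, 0% at 10%.
- 137 per arm, true difference 4: 66.7% at 2%, 24.7% at 5%, 0.5% at 10%.

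At 10% missing with 206 per arm, the best-worst case is significant in about 95% of trials with no effect, and the worst-best case stays significant in under 1% of trials with a true 4-point effect.

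**The literal standard-error reading.** With 206 per arm, 9.5/√206 = 0.66. The shift at 10% missing is then 4 × 0.66 × 0.10 = 0.26, or about 0.3 points.

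**What a graded analysis would show.** Opposite shifts of δ points in the two arms move the difference by 2δm. With 10% missing and about 185 observed per arm, the unadjusted standard error is 9.5 × √(2/185) = 0.99, so the 1% critical difference is 2.576 × 0.99 = 2.54. An observed 4-point difference loses significance at δ = (4 − 2.54)/(2 × 0.10) = 7.3 points. An observed difference of 0 becomes significant at δ = 2.54/0.20 = 12.7 points. Both tipping shifts lie inside the 19-point bound.

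**The case against.** The strongest reply is that these scenarios are deliberate bounds, offered as sensitivity analyses, and that bounds ought to widen as more data are missing. One bound turning significant under no effect is not a false-positive rate for any trial conclusion, because its mirror image is reported beside it. Agreement between them is strong evidence of robustness. All of that stands.

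A reader might infer from the shift formula that the verdict is set by missingness alone and that the scenarios can never show robustness. The figures do not support this: the verdict depends on effect and missing share together, the point estimates at the bounds still carry the effect, and agreement is common at 2% missing for effects of 0 or 4 points and at 5–10% for effects of 6–8 points. Nor does the article show that missingness here is high, because it gives no rate.

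A reader might also infer that the plan really intends a standard error. That is unlikely, since sections 4.1 to 4.3 and section 10 use SD only for the spread of scores. It is loose wording, though worth correcting when two analysts will work independently (section 9).

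Two further points limit the weight. The outcomes are declared exploratory in sections 11 and 14, and no primary estimate is affected. A narrow delta analysis would also say little: opposite 4-point shifts at 10% missing move the difference by only 2 × 4 × 0.10 = 0.8 points, and a 4-point result would become 3.2 against a critical value of about 2.5. The range has to be wider than that.

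What the reply does not supply is anything between multiple imputation and the 2-SD extremes.

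**Conclusion.** The point holds in a conditional form. With the plan's own SD and relevant difference, and equal missingness of about 10% or more per arm, the two scenarios will conflict for true effects of 0 and 4 points alike at the 1% level. The plan then has no analysis showing how large a departure is needed to change the conclusion. With about 2–5% missing, or an effect well above 4 points, the scenarios can agree and do their job. At alpha 0.001 with no effect, the crossing comes somewhat later (9.0% for metformin against placebo, 11.3% for an insulin pair).

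The conclusion rests on an assumed missing rate and, for the simulated shares, on an assumed baseline correlation of 0.5. The SD wording is a separate, minor defect that exists at any missing rate: the literal and the probable meaning differ by 3.8 against about 0.3 points at 10% missing. This is an inexpensive improvement to a sensitivity analysis, not a fault in the primary analysis.

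**What to change.** In section 7:

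1. Keep both scenarios and label them as outer bounds.
2. Define the imputed values as the group mean plus or minus *two SDs of the observed individual scores in that group*.
3. Add a delta-adjusted (tipping-point) multiple imputation under the primary regression model. Shift the imputed scores in each arm separately, in steps from 0 up to the 2-SD bound (about 18–19 points) or until the conclusion changes.
4. Report the tipping shift together with the share missing in each arm, so that it can be judged against the 4-point relevant difference.

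The cost is a paragraph of plan text, a few extra imputation runs on data already held and one more supplementary table. Section 12 says the data have not yet been inspected or analysed, so on the article's own account the change can still be prespecified.

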## Sample size and power considerations

4

Based on the sample size calculation in relation to the primary outcomes of the trial (change in mean intima media thickness of the common carotid arteries), we planned to include a total of 950 patients in the trial [1]. However, the trial was stopped due the end of the financing grant after the inclusion of a total of 412 participants [2,3]. For this factorial trial, this means that there is a comparison on 206 participants on metformin versus 206 participants on placebo and another comparison of three groups on different insulin regimens each including 137, 137, and 138 participants.

To increase the interpretability of the trial results and decrease the risks of random errors [14], we present power estimations for all planned outcomes [15]. We originally adjusted our threshold for statistical significance (the alpha value used in the sample size estimations) to 0.01 because of the multiple comparisons [1]. To take into account that the CIMT trial was stopped early (approximately halfway), we will now use an alpha value of 0.001 for the power estimations [14]. The following power estimations are based on the total 412 randomised participants for the metformin versus placebo comparison and a total of 274 randomised participants for each of the three pairwise insulin comparisons.

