### Analysis of quality of life and patient satisfaction

8.2

Primary analysis: linear regression adjusted for the baseline value and the three stratification variables age >65 years (yes/no), insulin treatment at trial entry (yes/no), and treatment at Steno Diabetes Center (yes/no) [1].

Secondary analysis: linear regression adjusted for the baseline value and the stratification variables (see above) and the design variables (sex (male/female), prior cardiovascular disease (yes/no), statin treatment at entry (yes/no), and glutamic acid decarboxylase antibodies (positive/negative)) [1]. We will in a supplementary analysis adjust for metformin administration before trial entry (yes/no).

All analyses will primarily include the modified intention-to-treat population. We will also perform the analyses adjusted for the stratification variables including the per-protocol population [1].

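### If multiple imputation is used, the listed predictors leave out the randomised arm and the baseline score; omitting the arm shrinks the questionnaire treatment effects by about the missing fraction

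*Protocol article*

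**What the plan says.** Section 7 (Handling of missing data) of the protocol article makes imputation conditional: "we will consider using multiple imputation if it is not valid to ignore missing data". It then fixes the status of the result: "If multiple imputation is used, then the primary result of the trial will be based on these data".

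The predictors are given in the last paragraph of that section: "We will use the three stratification variables used in the randomisation and the four predefined design variables during the multiple imputation procedure". The sentence continues "to estimate the missing values, i.e. age >65 years (yes/no), insulin treatment at trial entry (yes/no), and treatment at Steno Diabetes Center (yes/no") and goes on to sex, prior cardiovascular disease, statin treatment and glutamic acid decarboxylase antibodies. That makes seven binary variables. Metformin or placebo allocation, insulin regimen and the baseline questionnaire score do not appear. Nothing says that imputation is done separately by arm.

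Section 8.2 defines the model that the imputed data feed: "Primary analysis: linear regression adjusted for the baseline value and the three stratification variables". The coefficient of interest is the difference between arms.

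Section 7 also says that no missing values are expected for the time-to-event outcomes. The point therefore concerns the SF-36, ITSQ and Diab-Medsat only.

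**The concern.** An imputation model should contain at least the terms of the analysis model it serves. Here two terms are not named: the arm and the baseline score.

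Without the arm, a missing 18-month score is drawn from the pooled distribution whichever treatment the participant received. The imputed part of each arm then shows no difference between arms and dilutes the difference in the observed part. Without the baseline score, imputed values have no direct relation to the covariate on which the regression relies.

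The questionnaires carry most of the weight in the planned papers: section 11 places the main emphasis on them. Sections 4.1 to 4.3 set a 4-point minimal relevant difference, and section 8.1 uses it in the Trial Sequential Analysis. A true 4-point effect could therefore be reported below the plan's own threshold because of the imputation model alone. Two analysts working independently under section 9 would not expose this if both followed the same list.

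**Working it through.** **Inputs from the article.** The metformin comparison has 206 per arm (section 4: "there is a comparison on 206 participants on metformin versus 206 participants on placebo"). The SF-36 difference is 4 points, SD 9.5, alpha 0.001, stated power 83.0% (section 4.1).

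**Inputs assumed.** The article gives neither a questionnaire missing rate nor a baseline-outcome correlation. Missing fractions of 5 to 30% and a correlation of 0.5 are used for illustration.

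**1. The plan's own power figure.** The standard error is 9.5 × √(2/206) = 0.936, so 4/0.936 = 4.273. Two-sided power at 0.001 is Φ(4.273 − 3.291) = 83.7%. The noncentral t gives 83.0%, as stated. The power figures are not at fault.

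**2. Expected estimate when the arm is left out, data missing completely at random.** Let m1 and m0 be the missing fractions in the two arms, and let w = (1 − m1)/(2 − m1 − m0) be the share of observed participants who are in arm 1. Take the control mean as 0 and the treated mean as δ. Imputed values then have mean wδ in both arms.

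- Arm 1 mean: (1 − m1)δ + m1wδ
- Arm 0 mean: m0wδ
- Difference: δ[1 − m1(1 − w) − m0w]

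With m1 = m0 = m, w = ½ and the difference is δ(1 − m). For δ = 4 this gives 3.8, 3.6, 3.2 and 2.8 at 5, 10, 20 and 30% missing. With 30% against 10% missing, w = 0.7/1.6 = 0.4375 and the factor is 1 − 0.3 × 0.5625 − 0.1 × 0.4375 = 0.7875, or 3.15 points. With equal missingness the factor 1 − m also applies to each pairwise insulin comparison, because every arm is imputed with the same pooled mean.

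**3. Simulation, missing completely at random.** There were 412 participants, a true effect of 4, 5 imputations and 600 runs. The analysis model held arm, baseline and three stratification variables. Monte Carlo error is about 0.03 to 0.04. Mean estimates:

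| Imputation predictors | 10% | 20% | 30% |
|---|---|---|---|
| Seven listed | 3.55 | 3.19 | 2.85 |
| Seven + baseline | 3.56 | 3.19 | 2.82 |
| Seven + arm | 3.97 | 4.00 | 4.07 |
| Seven + arm + baseline | 3.97 | 3.98 | 4.05 |
| Complete cases | 3.96 | 3.99 | 4.06 |

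The shrinkage comes from the arm alone. Adding only baseline does not remove it; adding only the arm does. At 30% against 10% missing the seven-variable list gave 3.12, against the expected 3.15.

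**4. Simulation, missingness dependent on baseline.** Participants with lower baseline scores were more often missing. Rates are for a participant with an average baseline, arm 1 / arm 0.

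| Imputation predictors | 30/10, true 4 | 10/30, true 4 | 30/10, true 0 |
|---|---|---|---|
| Seven listed | 3.51 | 2.55 | 0.55 |
| Seven + arm | 4.62 | 3.33 | 0.72 |
| Seven + arm + baseline | 3.96 | 3.99 | 0.07 |

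Here the omitted baseline score adds a bias of its own, in either direction, and it produces an apparent effect when there is none.

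**5. Effect on power.** Putting the shrunken differences into the formula in step 1 gives about 78%, 71%, 55% and 38% at 5, 10, 20 and 30% missing. This ignores imputation variance. A simulation with 20 imputations and Rubin's rules at 20% missing gave power at 0.001 of 49% with the seven variables and 85% with arm and baseline added; at 0.01 it was 80% and 97%. These levels gain from baseline adjustment at correlation 0.5, so they should be compared with each other and not with the plan's 83.0%.

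**The case against.** The strongest reply is that the sentence does not say the seven variables are the only ones. It may simply spell out which stratification and design variables are meant, with arm and baseline taken for granted. Section 7 also defers to a cited recommendation that cannot be checked here. This stands as doubt about intent. It does not cure the text: the article nowhere puts the arm or the baseline score into the imputation, and the enumeration reads as a definition, so an analyst following it literally would leave them out. Nor is this a detail left to a fuller document, since the article itself fixes the list.

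Second, imputation is only considered when missing data cannot validly be ignored. Under the completely random missingness of step 3, the plan might well keep the complete-case analysis, which is unbiased there. That is right and limits the claim. But when imputation is used its result is primary, and step 4 shows the list also fails when missingness depends on baseline.

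Third, all outcomes are declared exploratory (sections 11 and 14), and at 5% missing the loss is only 0.2 points. Both are true and bear on the size of the harm. The best-worst and worst-best scenarios do not help, because they are sensitivity analyses and leave the primary estimate as it is.

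A reader might go further and infer that the trial's primary questionnaire results will be biased toward no effect, and that both omissions cause this. The documents do not support that. Imputation may never be triggered, the missing rate is not given, proportional shrinkage comes from the arm only, and the omission of baseline can push the estimate either way.

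**Conclusion.** The concern holds in conditional form and is wrong as written. If multiple imputation is used with the seven listed variables and no others, omitting the arm multiplies the questionnaire treatment effect by one minus the missing fraction, given data missing completely at random and equally by arm. That factor does not depend on the assumed correlation; the simulated power figures and the results under baseline-dependent missingness do. The baseline omission is a separate fault of incompatibility with the section 8.2 model, with no fixed direction of bias. The actual size cannot be stated, because the article reports no questionnaire missing rate.

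**What to change.** Add one sentence to section 7: the imputation model will include both randomised factors (metformin or placebo, and insulin regimen), the baseline score of the same instrument and all covariates of the analysis model, in addition to the seven listed variables. Imputing separately by arm is an alternative to including the arm as a predictor. Coded arm labels are enough, so the blinded analysis in section 9 is kept. Scores on the other instruments may be added as auxiliary variables, but they are optional: arm and baseline alone restored the estimate to about 4.0.

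The cost is that sentence and a longer predictor list. The primary analysis already needs the arm and the baseline score, so no new data are required. The change should be made before the data are inspected.
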